## Abstract

**Background:**

Facial neuromuscular retraining (fNMR) is a noninvasive physical therapy widely used to treat peripheral facial palsies. It consists of different intervention methods that aim to reduce the debilitating sequelae of the disease. Recently, the use of mirror therapy in the acute facial palsy and postsurgical rehabilitation contexts has shown promising results, suggesting its use as an adjunct to fNMR in treating patients with later stages of paralysis, such as the paretic, early, or chronic synkinetic.

**Objective:**

The main aim of this study is to compare the efficacy of an added mirror therapy component with fNMR in patients with peripheral facial palsy (PFP) sequelae in 3 different stages. The specific objectives of this study are to measure the effects of combined therapy compared to fNMR alone on (1) participants’ facial symmetry and synkinesis, (2) quality of life and psychological aspects of the participants, (3) motivation and treatment adherence, and (4) different stages of facial palsies.

**Methods:**

This study is a randomized controlled trial that compares the effect of fNMR combined with mirror therapy (experimental group: n=45) with fNMR alone (control group: n=45) in 90 patients with peripheral facial palsy presenting with sequelae 3-12 months after onset. Both groups will receive 6 months of rehabilitation training. Facial symmetry and synkinesis; participants’ quality of life; and their psychological factors, motivation, and compliance will be assessed at baseline (T0), 3 months (T1), 6 months (T2), and 12 months (T3) postintervention. Outcome measures are (1) changes in facial symmetry and synkinesis assessed with facial grading tools, (2) quality of life changes with patient questionnaires, and (3) therapy motivation with a standardized scale, as well as adherence to treatment with metadata. Changes in facial symmetry and synkinesis will be judged by 3 assessors blinded to group assignment. Mixed models and Kruskal-Wallis, chi-square, and multilevel analyses will be conducted according to the appropriate variable type.

**Results:**

Inclusion will start in 2024 and is anticipated to be completed in 2027. The 12-month follow-up will be completed with the last patient in 2028. We expect patients included in this study to experience improvement in facial symmetry, synkinesis, and quality of life, regardless of group assignments. A potential benefit of mirror therapy for facial symmetry and synkinesis could be noted for patients in the paretic phase. We hypothesize better motivation and adherence to treatment for the mirror therapy group.

**Conclusions:**

The results of this trial may provide new guidelines for PFP rehabilitation with patients dealing with long-term sequelae. It also fills the need for robust evidence-based data in behavioral facial rehabilitation.

**International Registered Report Identifier (IRRID):**

PRR1-10.2196/47709

## Introduction

### Background

Peripheral facial palsy (PFP) with sequelae is a debilitating condition that can significantly impact a patient’s quality of life due to functional, social, and psychological factors [1]. Facial asymmetry and the inability to express emotions and smile adequately can make communication challenging, leading to high levels of social problems, frustration, anxiety, and depression [1]. In nonflaccid facial palsy, patients may have hyperkinesis, muscle contracture, and synkinesis, which can affect normal activities such as drinking, eating, and articulating and can cause embarrassment and, in some cases, facial pain [2,3]. Therefore, providing adequate interventions to help patients deal with these issues is essential. Physical therapy is a type of nonsurgical treatment shown to help manage the sequelae previously mentioned in patients with nonflaccid chronic peripheral facial palsy [4]. Optimal facial rehabilitation modalities could also differ depending on the stage of nonflaccid PFP [5]. Although there are no generally accepted guidelines for the different stages, some authors define the paretic phase as recovery from 3 to 6 months after onset, while the early synkinetic phase would be defined as 6 to 9 months after onset [5,6]. The chronic synkinetic phase would begin at 9 months after onset, as defined by Beurskens et al [7].

### Facial Neuromuscular Retraining

Mime therapy [8,9] and facial neuromuscular retraining (fNMR) [10] are 2 rehabilitation techniques for managing facial palsy sequelae that stand out in the literature [11]. Mime therapy consists of facial massage and specific facial retraining to coordinate both hemifaces by using emotional cues to express a particular facial movement or by starting to use a specific muscle to create an expression [8]. Similarly, fNMR consists of relearning motor patterns to improve facial movements through conscious, consistent, and slow selective activation of facial muscles using individualized training programs made by qualified facial therapists [12]. This therapy aims to normalize facial muscle functions by inhibiting synkinetic contractions and improving resting tone altered by contractures [13]. In the literature, these 2 therapies have recently merged into one called fNMR, which combines techniques such as soft tissue massage, biofeedback, education, relaxation, and selective movement retraining [14]. fNMR is considered a well-supported approach that has been studied in many cohort studies [14].

### Mirror Therapy in Facial Rehabilitation

Mirror therapy is a form of motor therapy that involves placing a mirror in the patient’s midsagittal plane, reflecting the unaffected limb or body part onto the affected one, creating the illusion of normal movements on the absent or affected side [15]. It is based on the brain’s ability to undergo cortical reorganization [15]. The first clinically reported effects of mirror therapy were pain reduction in arm amputees and alleviation of hemiparesis [16]. Since then, this therapy has been used in other contexts, including facial rehabilitation and uses specific computer software to replicate the unaffected side over the affected side [17] (Figure 1).

**Figure 1 figure1:**
[figure not shown]
Representation of the setting with mirror therapy for facial rehabilitation. (A) Patient sits in front of the computer with a webcam. (B) Visual biofeedback of modified face.

A recent study investigated the effects of mirror therapy over 3 months on 32 patients diagnosed with facial nerve palsy less than 12 months after acoustic neuroma resection surgery [17]. The control group received traditional rehabilitation with mime therapy, while the experimental group had to perform an additional weekly session of mirror therapy using specific software and motor imagery exercises with different emotions or gestures. Both groups were evaluated for facial symmetry using the House-Brackmann Facial Nerve Grading system [18], Sunnybrook [19], and Facial Clinimetric Evaluation (FACE) [20]. Although every subject demonstrated improvement in facial symmetry, the experimental group showed significantly better results than the control group for House-Brackmann scores and quality of life. In a recent case report, mirror therapy and motor imagery were used with a small group of patients (n=5) with chronic facial palsy to reduce synkinesis, which resulted in the reduced muscular activity of synkinetic muscles with mirror therapy [21].

A recent longitudinal study recruited patients with Bell palsy within 14 days of onset and followed them for 1 year [22,23]. The control group received only basic counseling in their rehabilitation, while the experimental group followed a new protocol called the Mirror Effect Plus Protocol (MEPP), which was mainly based on mirror therapy [24] and motor imagery [25]. One year after onset, significant results included less synkinesis development, increased facial symmetry, and improved self-reported quality of life in the experimental group [23]. Although the MEPP shows interesting results in patients with Bell palsy when initiated in the acute phase, to our knowledge, there is very limited evidence for mirror therapy as an effective treatment tool for patients presenting with long-standing peripheral facial paralysis from different etiologies.

### Expected Effects of Rehabilitation Techniques

Based on the work of Diels and Beurskens [14], fNMR is expected to improve facial symmetry and reduce synkinesis in long-standing facial palsy. Increased resting tone on the patient’s affected side often creates muscle tightness or contractures, leading to decreased range of motion, alteration of facial expressions, and patient discomfort. Therefore, soft tissue mobilization and specific facial manipulations can reduce such tightness and increase facial symmetry at rest [14]. To inhibit synkinesis, the therapy seeks to recognize abnormal movement patterns and uses different strategies to reduce them while activating desired facial muscles [5]. Patients must be instructed to perform slow, small, and controlled facial expressions or movements. As the patient’s control improves and the synkinesis movements remain suppressed, the range of motion, facial function, and symmetry are believed to improve [14]. As proprioceptive input is absent in facial muscles, fNMR uses different education and biofeedback strategies, such as surface electromyography and touch, to help patients focus on the right muscle contraction. Although successful results have been demonstrated in the past with patients in the chronic phase, more randomized controlled trials are required to assess its efficacy [4]. It has been noted that when traditional mirrors are used in practice sessions as biofeedback, the mismatch between the motor command and the visual feedback associated with the affected side might result in maladaptive muscle hyperactivity and compensation, which is counterproductive with fNMR [26,27]. In this context, adding mirror therapy during practice is an interesting idea because it might avoid such discrepancies between motor command and sensory input [23]. However, the potential added value of mirror therapy for long-standing facial palsies remains to be proven.

### Study Aims

There is a growing interest in exploring the effect of adding mirror therapy as a biofeedback tool in fNMR, particularly in patients with peripheral facial palsy dealing with sequelae 3-12 months after onset. Therefore, the general aim of this protocol is to compare the potential effects of adjunctive mirror therapy with the gold standard fNMR on facial function and rehabilitation in nonflaccid facial paralysis. The specific objectives of this study are (1) to measure the effects of combined therapy compared to fNMR alone on participants’ facial symmetry and facial synkinesis, (2) to measure the effects of combined therapy versus fNMR alone on the quality of life and psychological aspects of the participants, and (3) to measure the effects of combined therapy versus fNMR alone on motivation and treatment adherence.

## Methods

### Eligibility Criteria

To be included in the study, patients must be 18 years or older, experiencing their first PFP, be from 3 months to 12 months after onset, and must have a score 4 or 5 on Facial Nerve Grading System 2.0 (FNGS 2.0) [28]. In addition, they must have sufficient cognitive status, measured by a cutoff score of 23 on the Montreal Cognitive Assessment [29,30], and present with no active mental health diagnosis. They should also not present with a history of neurologic diseases affecting facial function. Patients with concomitant therapies or botulinum toxin type A injections, presenting with bilateral palsies or with medically uncontrolled metabolic diseases, will be excluded from the study. Access to an internet connection and basic computer literacy will also be verified as eligibility criteria.

### Recruitment and Compensation

As determined, thanks to a power calculation measure based on Martineau et al [22] to reach a power of 0.8 with a size effect of 0.6 and an α of .005, 90 patients with peripheral facial palsy of diverse etiologies in the paretic (n=30), early synkinetic (n=30), or chronic synkinetic phase (n=30) will be recruited to the study. They will then be randomized into 2 groups, mirror therapy plus fNMR or fNMR alone, by computerized block randomization. No compensation or incentive is planned to be provided at this time. Recruitment is planned to be conducted in 3 tertiary care centers (hospitals) in Canada, England, and Belgium (Hôpital Maisonneuve-Rosemont, Queen Victoria Hospital, and Sint-Augustinus GZA Hospital, respectively). A telehealth option will be available for the participants via institutionally secured platforms.

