Finally, we anticipate that patients in the mirror therapy group will exhibit better treatment adherence compared to those undergoing fNMR alone. Adherence to facial retraining has been shown to be influenced by various factors, including time constraints due to other daily activities and accessibility to the training facilities [43]. Facial therapists often overestimate their patients’ commitment to the facial rehabilitation process, with data indicating that only 30% of patients fully comply [43]. Nonadherence to therapy can impact treatment outcomes, highlighting the importance of measuring adherence in this study. Objective measures of adherence using metadata will be used, providing strength compared to relying solely on subjective measures of compliance. Subjective measures of compliance (such as patient questioning) may be influenced by patients’ memory or perceptions [44]. Furthermore, the postpandemic shift toward telehealth for service delivery may facilitate adherence [44]. In this study, we will document whether participants received care via telehealth and examine whether this factor appears to influence compliance.

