### Strengths and Limitations

The primary strength of this protocol lies in its international multicentric collaboration, which will facilitate the examination of a substantial number of participants representing diverse etiologies of peripheral facial nerve palsy (n=90, with 45 patients per group). The randomized controlled trial design used in this study allows for assessing the potential additional benefits of incorporating mirror therapy into the rehabilitation of PFP. This investigation has the potential to contribute to an evidence-based approach for clinicians involved in the care of these patients.

However, the study design does have certain limitations. First, it is not feasible to blind both the patients and treating clinicians to the assigned conditions, which could introduce bias in terms of motivation and perception of treatment efficacy. To mitigate these risks, blinded judges will be involved in assessing participants, and therapists will use a standardized feedback approach in both therapy sessions and assessments. Additionally, using Emotrics will allow for more objective facial metrics at each assessment time point [33,45]. Second, the inclusion of paretic patients in the study poses a potential confounding factor due to the occurrence of spontaneous recovery in certain cases of facial palsy [3]. However, the large number of participants and their enrollment at least 3 months after the onset of symptoms should help mitigate potential biases. It is worth noting that in Bell palsy, the most common cause of PFP, approximately 70% of patients experience full recovery within 3 months of onset [3]. The advantage of including patients across such a broad timeframe (3-12 months after onset) is to recruit a cohort that is as representative as possible of the clinical reality of facial rehabilitation in different countries.

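### Reading α as .05, 90 is the bare minimum for 80% power and also the number recruited, so the stated power assumes essentially complete 6-month data

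*Protocol article*

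**What the plan says.** Under Recruitment and Compensation, the protocol article reports a power calculation "to reach a power of 0.8 with a size effect of 0.6 and an α of .005, 90 patients". The sentence goes on to split these patients by phase: "in the paretic (n=30), early synkinetic (n=30), or chronic synkinetic phase (n=30) will be recruited to the study". The next sentence randomises them to two groups. Strengths and Limitations repeats the count as "n=90, with 45 patients per group", and the Methods paragraph of the abstract also gives 45 and 45.

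Statistical Analysis ties the calculation to the primary outcome, the change from baseline to 6 months (T2). It plans a mixed model over the assessment times for the continuous measures. The article states no expected loss before T2 and no enlargement of the sample for it. It also does not name the test behind the calculation, its sidedness, or the metric of the effect size.

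**The concern.** A power calculation gives the number of patients who must contribute an outcome. Here the same figure serves as the number recruited. The two agree only if nobody is lost between randomisation and T2.

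The issue is what the published figure means, not only that an attrition rate is absent. The article commits itself to "to reach a power of 0.8" from 90 recruited patients. If some have no T2 assessment, the power is lower than the sentence says, and a non-significant 6-month comparison could be given more weight than the design supports.

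**Working it through.** **Inputs.** Power 0.8, effect size 0.6, α .005 and N = 90 come from Recruitment and Compensation. The 45 per arm comes from the abstract and from Strengths and Limitations. Two assumptions are mine: 0.6 is a standardised mean difference between the two arms, and the test is a two-sample comparison of means.

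**Step 1: reproduce 90.** The normal approximation per arm is n = 2(z₁₋α/₂ + z₀.₈)² / d².

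- α .005, two-sided: 2(2.807 + 0.842)² / 0.36 ≈ 74.0, so 74 per arm
- α .05, two-sided: 2(1.960 + 0.842)² / 0.36 ≈ 43.6, so 44 per arm

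Totals for both arms, with the exact noncentral t alongside:

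| α | Sides | Normal approximation | Exact t |
|---|---|---|---|
| .005 | two | 148 | 152 |
| .005 | one | 130 | 134 |
| .05 | two | 88 | **90** |
| .05 | one | 70 | 72 |

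Reading 0.6 as Cohen's f with 2, 3 or 6 groups gives totals of about 24 to 42 at α .05 and 42 to 64 at α .005. Among these readings, only the two-sided t-test at α .05 returns 90. Its unrounded requirement is 44.6 per arm.

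**Step 2: power with fewer T2 outcomes.** For the t-test, the noncentrality is d√(n₁n₂/(n₁+n₂)) with n₁+n₂−2 degrees of freedom. With 45 + 45 this is 0.6 × √22.5 = 2.846 on 88 degrees of freedom. At two-sided α .05:

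| Patients with T2 outcome | Power (exact t) |
|---|---|
| 45 + 45 | .804 |
| 45 + 44 | .799 |
| 44 + 44 | .795 |
| 43 + 43 | .785 |
| 10% loss (40.5 per arm) | .760 |
| 15% loss (38.25 per arm) | .736 |
| 20% loss (36 per arm) | .709 |

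The loss rates are assumptions, taken as equal in both arms. By the normal approximation, power is .812 at 45 + 45, .803 at 44 + 44 and .794 at 43 + 43.

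**Step 3: the printed α.** At two-sided α .005, power with all 90 is .490 (exact t) or .516 (normal approximation). After 10% loss it is .431 (exact t).

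**The case against.** **A condensed article may leave attrition to the full protocol.** This is fair as far as a withdrawal rate or a replacement rule goes, and neither absence is counted here. What remains is a published statement that joins inputs, result and number recruited in one sentence. On the only reading tried that reproduces the result, that result contains no reserve.

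**The figures use an α that is not printed.** Correct, and this limits the point. At .005 the design falls far short of 0.8 with no loss at all, which is the larger defect in the sentence. Correcting .005 to .05 does not remove the present point, because 90 is then exactly the requirement.

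**A margin might be hidden.** A one-sided test at .05 needs 72, and 72 / 0.80 = 90 would contain a 20% allowance. The article mentions neither one-sided testing nor such an allowance, so this stays a conjecture. It is nevertheless a reason to have the test named. The total may also have been rounded up from 88 to three phases of 30, which would leave two spare patients.

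**A reader might infer that any loss breaks the claim.** That is too strong. One loss moves the t-test from .804 to .799, and by the normal approximation 44 + 44 still reaches .803. As the article gives power to one decimal, even .760 would round to 0.8.

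**The planned analysis is a mixed model.** It can use baseline and 3-month data from patients who miss T2, so the complete-case figures may overstate the loss of power. How much is recovered cannot be computed from the article.

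**A reader might also cite the article's figure that only 30% of patients fully comply as a sign of withdrawal.** It does not show that. It describes compliance with rehabilitation, and a patient who skips home exercises can still attend T2. The remark "Nonadherence to therapy can impact treatment outcomes, highlighting the importance of measuring adherence in this study" likewise concerns adherence, not missing outcomes. The absence of compensation gives no loss rate either.

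**Conclusion.** The point holds in a limited form. If α is .05 two-sided and 0.6 is a standardised mean difference, 45 per arm is the bare minimum for a two-sample t-test. The stated 0.8 then assumes essentially complete T2 data. The shortfall is negligible for one or two losses, about 4 percentage points at 10% loss (.804 to .760), 7 at 15% (.804 to .736) and between 9 and 10 at 20% (.804 to .709). These are complete-case figures under assumed loss rates, and the mixed model may reduce the shortfall.

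The article does not support saying that substantial withdrawal is expected or that every single loss matters. It also does not show that the trial has any particular policy on replacing patients who withdraw.

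**What to change.** Deal with this together with the α. First correct or confirm the .005. Then, in the same sentence of Recruitment and Compensation, name the test and its sidedness, and give the power for the number expected to have a T2 assessment under a stated loss rate. If α is .05, the wording could be: *90 patients will be randomised; with a two-sided two-sample t-test at α .05 and a standardised difference of 0.6, power is 80% with complete T2 data, about 76% if 10% and about 71% if 20% have no T2 assessment.* If .005 is confirmed, these figures do not apply and must be recalculated, because power is then about 49% before any loss.

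Enrolment, the 45/45 allocation and the phase quotas can stay as they are, and no rule on replacement needs to be added. The cost is wording only, plus a somewhat less favourable stated power.

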### Statistical Analysis

As mentioned, a power calculation was done based on a previous study [23] for the primary outcome (changes from baseline to 6 months). Every measure of facial symmetry and synkinesis will be judged by 3 assessors, blinded to group assignment. Intraclass correlation coefficients will be calculated to ensure interrater reliability, and the resulting means of the assessors’ findings will be used for further statistical analysis. We will first gather descriptive statistics to provide summary data. Then, for continuous variables (Emotrics measurements, Sunnybrook global score, FNGS 2.0 global scores, FACE score, FDI, and intrinsic motivation inventory), a mixed model analysis with patients as random variables and time+group assignment as fixed variables will be considered, with auto-regressive covariance structure, given the structure of the time points for the assessments. Comparison between the timing of recruitment after PFP onset (3-6 months after onset vs 6-9 months vs 9-12 months) and outcomes at T2 and T3 will be specifically measured using multilevel analysis. Kruskal-Wallis analyses will be considered for ordinal variables (synkinesis subscores, symmetry subscores, and motivation subscores). Finally, chi-square analysis will be considered for dichotomous variables (adherence yes or no). Data will be encoded with Excel sheets, and SPSS (IBM Corp) will probably be used for statistical analysis.

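### The stated α of .005 does not fit the stated power, effect size and 90 patients under a standard two-sample calculation, whereas α .05 does

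*Protocol article*

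**What the plan says.** The sample size statement is in Methods, Recruitment and Compensation: "to reach a power of 0.8 with a size effect of 0.6 and an α of .005, 90 patients with peripheral facial palsy". The same section gives the comparison: "They will then be randomized into 2 groups, mirror therapy plus fNMR or fNMR alone, by computerized block randomization". Strengths and Limitations confirms the split as "n=90, with 45 patients per group", and the Abstract gives the same 45 and 45.

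The Statistical Analysis section returns to the calculation and says that "a power calculation was done based on a previous study [23] for the primary outcome (changes from baseline to 6 months". Recruitment and Compensation instead credits the calculation to reference 22.

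The article does not say which test the calculation assumed, whether α is one- or two-sided, or on what scale the 0.6 is expressed. The value .005 appears once and is not explained, for example as an adjustment for multiple comparisons.

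**The concern.** Power, effect size, α and sample size are tied together: once the test is fixed, any three determine the fourth. A threshold of .005 is ten times stricter than the usual .05 and normally calls for a much larger trial. Ninety patients is a familiar total for an effect of 0.6 at α .05, so .005 looks out of place beside it.

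The value matters because it is the only significance threshold in the article. If results are judged at .005 as printed, the chance of detecting the effect the trial was sized for is well below the stated 80%, unless some unstated feature of the analysis makes up the difference. If results are judged at .05, the analysis will depart from the published threshold, and nothing in the article would show that .05 had been meant from the start.

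**Working it through.** **Inputs from the article.** Power 0.8, effect size 0.6, α .005 and 90 patients (Recruitment and Compensation); 45 per arm (Strengths and Limitations).

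**Assumptions.** The 0.6 is a standardised mean difference d (SD = 1), and the test is an unadjusted comparison of two independent means. Both sidednesses were tried.

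**Step 1. Try to reproduce 90 at α .005.** Normal approximation:

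n per arm = 2 × (z for α + z for power)² / d²

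- Two-sided .005: 2 × (2.807 + 0.842)² / 0.36 = 73.96, so 74 per arm, 148 in total.
- One-sided .005: 2 × (2.576 + 0.842)² / 0.36 = 64.9, so 65 per arm, 130 in total.

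The noncentral t distribution gives 76 per arm (152) two-sided and 67 per arm (134) one-sided. None of these is 90.

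**Step 2. Change only α, to two-sided .05.**

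- Normal approximation: 2 × (1.960 + 0.842)² / 0.36 = 43.6, so 44 per arm, 88 in total.
- Noncentral t: 44.6, so 45 per arm, **90 in total**, which is the stated figure.

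**Step 3. Power with 45 per arm and d = 0.6.** Noncentrality = d × √(n/2) = 0.6 × √22.5 = 2.846, with 88 degrees of freedom.

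| α | Critical t | Power (t) | Power (normal) |
|---|---|---|---|
| .05 two-sided | 1.987 | 0.804 | 0.812 |
| .005 two-sided | 2.880 | 0.490 | 0.516 |
| .005 one-sided | 2.633 | 0.586 | 0.607 |

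**Step 4. Effect detectable with 80% power, 45 per arm, two-sided t.** About 0.60 SD at α .05 and about 0.79 SD at α .005.

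**Step 5. Other readings at α .005.**

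- A Mann-Whitney test (efficiency 0.955) needs 76 / 0.955 = 79.6, so about 80 per arm, 160 in total.
- Taking 0.6 as Cohen's f gives a total of 42 (two groups), 49 (three groups) or 64 (six cells, 5 df).
- A paired t test gives 41.

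None gives 90.

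**Step 6. What would make the four figures agree.** Adjusting for baseline with correlation r raises the effective d to 0.6 / √(1 − r²). Setting this equal to the 0.787 detectable at two-sided .005 gives 1 − r² = (0.6 / 0.787)² = 0.581, so r is about 0.65. At r = 0.5 the power is 0.66, at 0.6 it is 0.75 and at 0.7 it is 0.86. The article states no such correlation.

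**The case against.** The strongest reply is that the mismatch rests on a test the article never names. Statistical Analysis plans a mixed model over repeated assessments, and an analysis that uses the baseline value can need fewer patients than a plain t test. With a correlation of about 0.65 or more, 90 patients would give 80% power at .005. This stands to the extent that a reader might infer the four figures are mathematically incompatible, and the documents do not support that. What can be said is that they do not agree under the standard calculation, and that the article gives no correlation or method to bridge the gap.

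A second reply is that .005 is most likely a one-digit slip, in which case the sample size is sound. That also stands. A reader might infer from 49% that the trial has half the power it claims, but this follows only if .005 is the intended threshold. The exact match to 90 at .05 points the other way.

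A reader might also want to extend the point to the lack of an attrition allowance, the unnamed outcome measure behind the 0.6, or the choice of a primary scale. The article is silent on these rather than wrong, and a condensed article may leave such detail to the full protocol or analysis plan. They have no bearing on whether the four figures agree.

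**Conclusion.** The sample size statement is wrong as written or lacks an assumption it depends on. Under an unadjusted comparison of two means with d = 0.6 and 45 per arm, α .005 gives about 49% power two-sided or 59% one-sided, against a stated 80%. About 76 per arm (67 one-sided) would be needed, and the effect detectable with 80% power is about 0.79 SD (two-sided) rather than 0.6.

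The result depends on reading 0.6 as a standardised mean difference. The article does not say so, but that reading with two-sided α .05 returns exactly 90, which no other reading tried at .005 does. A misprint for .05 is therefore the probable explanation, though the article alone cannot settle it. Either way, the published threshold and the published power should not stand together without correction or justification.

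**What to change.** Amend the sentence in Recruitment and Compensation in one of these ways:

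- **If .05 was intended:** write two-sided α of .05. The other three figures can stay.
- **If .005 was intended:** keep 90 patients and restate the power as about 0.49 for a standardised difference of 0.6 (two-sided t test), or restate the detectable effect as about 0.79 SD at 80% power.
- **If .005 and 80% are both intended, on the strength of an adjusted or repeated-measures analysis:** name the test and give the assumed baseline or repeated-measures correlation (about 0.65 or more) with its source.

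The cost is one or two sentences. None of the three changes the number of patients. Under the second, a published figure becomes less favourable. Under the third, the authors must be able to support the correlation.
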